**Reporting and management of adverse events**

Serious Adverse Events (SAE) involve any untoward occurrence that results in death, is life-threatening, requires hospitalisation or prolongation of existing hospitalisation, results in persistent or significant disability or incapacity, or is otherwise considered medically significant by the investigator. Due to the nature of the intervention, we do not anticipate SAE. MSVR champions will be encouraged to discuss with participants whether they have experienced any problems or accidents at work based on the information provided during the intervention.

Related unexpected serious adverse events (RUSAE) will be any SAE where, in the opinion of the Principal Investigator (PI), the event was considered to be (1) “related” that is, it resulted from the administration of any of the research procedures, and (2) “unexpected” that is, the type of event is not listed in the protocol as an expected occurrence. In the case of this study, it could involve accidental injury resulting from workplace adaptations recommended by the MSVR champion, or workplace accidents resulting in injury requiring hospital treatment.

This data will be collected by self-report (participant questionnaires and ad-hoc CRFs, or via sites notifying a member of the research team). Any event that, in the opinion of the PI, is “related” (resulted from the administration of the research procedure) and “unexpected” (the type of event is not listed as an expected occurrence) will be reported to the research ethics committee within 7 days of being informed of such events. Fatal and life-threatening events will be reported no later than 3 calendar days after the sponsor or PI is first aware of the event. Any other additional relevant information will be reported within 7 calendar days of the initial report.

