**Intervention: MSVR**

The full description of the intervention is presented elsewhere [13]. Due to feedback from previous studies [15], the intervention was extended to support the person with MS over six months (instead of the original three months).

MSVR will be delivered by employees from MS charities currently working within MS charities supporting people with MS with advocacy or information provision. These employees have a wide range of professional backgrounds, expertise in MS (including symptoms and progression), skills with active listening, and have been trained to handle difficult conversations. The workers from MS charities, called “MSVR Champions”, will receive training and mentoring in preparation for the trial.

MSVR for people with MS involves an initial interview (including vocational goal setting), followed by up to 10 hours of individually tailored support according to need. The support will focus on supporting the person with MS to meet their vocational goals by addressing topics such as:

- Understanding MS
- Advice on reasonable adjustments (e.g., modification to the work environment or duties to accommodate the impact of MS)
- Support requesting reasonable adjustments
- Fatigue management
- Managing cognition at work
- Information about legal rights
- Disclosure (i.e.., telling the employer or colleagues about the MS diagnosis)
- Long-term career planning (i.e., exploring alternative career options)
- Managing mood difficulties
- Signposting to local and national resources.

The intervention addresses the individual needs of the person with MS and offers advice remotely (e.g., via telephone, videoconference, or email). The sessions will be arranged at a time convenient for the person, and the support needed will vary according to the complexity of their workplace difficulties. Participants will receive a brief written summary of the content discussed in each session via email with further resources to complement the knowledge gained.

MSVR for the employers will involve an initial interview (approximately 30 minutes) to understand their experiences supporting the employee with MS and up to 4 hours of support over the six-month intervention. The employer’s intervention includes:

• Signposting to relevant organisations.

• Educational resources.

• Information about MS and invisible symptoms.

• Support with providing reasonable adjustments.

• Legal responsibilities (Equality Act).

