**Table 2 Summary of assessments and time points**

| Activities / Measures | Assessment and time-point | | | | | | |
| --- | --- | --- | --- | --- | --- | --- | --- |
|  | **Screening** | **Baseline**  **(A1)** | **Intervention** | **End of Intervention**  **(A2)** | **3 months FU** | ***6 months***  ***FU*** | ***12 months***  ***FU*** |
| Screening for eligibility | x |  |  |  |  |  |  |
| Completion of consent form | x |  |  |  |  |  |  |
| Demographic information | X |  |  |  |  |  |  |
| Randomisation | x |  |  |  |  |  |  |
| Goal Attainment Scaling |  | x | **MSVR Intervention** | x | x | x | x |
| 36-item short form health survey |  | x |  | x | x | x | x |
| Perceived Difficulties Questionnaire |  | x |  | x | x | x | x |
| Work Productivity and Activity Impairment Questionnaire for MS |  | x |  | x | x | x | x |
| Modified Fatigue Impact Scale -5 Items version |  | x |  | x | x | x | x |
| EQ-5D-5L |  | x |  | x | x | x | x |
| Generalised anxiety disorder scale |  | x |  | x | x | x | x |
| Patient health questionnaire 8-item scale |  | x |  | x | x | x | x |
| General self-efficacy scale |  | x |  | x | x | x | x |
| Workplace Accommodations questions |  | x |  | x | x | x | x |
| Resource use questionnaire |  | x |  | x | x | x | x |
| Adverse events |  |  | x |  |  |  |  |
| Intervention cost (training, mentoring, intervention delivery) |  |  | x |  |  |  |  |
| Acceptability of MSVR (interviews with people with MS and employers) |  |  |  | x |  |  |  |
| Acceptability of training (MSVR champion questionnaire) | x |  |  |  |  |  |  |
| Acceptability of MSVR and mentoring (interviews with MSVR Champions) |  |  |  | x |  |  |  |
| A=Assessment; FU= Follow-up; EQ-5D= European Quality of Life- 5D; MS= multiple sclerosis; MSVR= Multiple Sclerosis Vocational Rehabilitation | | | | | | | |

The outcome measures will be collected using REDCap, or by post or telephone if a participant cannot access an electronic device. The acceptability measures (i.e., interviews) will be collected remotely via telephone or Microsoft Teams. To minimise missing data, we will set up a REDCap email notification to automatically remind participants to complete the questionnaires 2 weeks from the due date.

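### No defined adverse event covers a work-related harm of MSVR advice, so such harms could go uncounted or be ascertained in one arm only

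*Protocol*

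**What the plan says.** The Protocol section Reporting and management of adverse events defines two categories.

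- **SAE.** The definition opens "Serious Adverse Events (SAE) involve any untoward occurrence that results in death, is life-threatening, requires hospitalisation or prolongation of existing hospitalisation" and closes with an event that "results in persistent or significant disability or incapacity, or is otherwise considered medically significant by the investigator".
- **RUSAE.** "Related unexpected serious adverse events (RUSAE) will be any SAE where, in the opinion of the Principal Investigator (PI") judges the event both related to the research procedures and unexpected. For this trial, the section says that "it could involve accidental injury resulting from workplace adaptations recommended by the MSVR champion, or workplace accidents resulting in injury requiring hospital treatment".

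The same section encourages champions to discuss with participants "whether they have experienced any problems or accidents at work based on the information provided during the intervention". It names participant questionnaires, ad-hoc CRFs and notification by sites as the collection routes. A later sentence requires related and unexpected events to go to the ethics committee, and this sentence does not repeat the word serious.

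Table 2 has a row headed "Adverse events", marked only in the Intervention column. The protocol does not define a non-serious adverse event.

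Among the topics listed under Intervention: MSVR are "Disclosure (i.e.., telling the employer or colleagues about the MS diagnosis)" and "Long-term career planning (i.e., exploring alternative career options)", together with help in asking the employer for adjustments.

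**The concern.** MSVR acts on a person's employment, and everyone enrolled is in paid work. If the advice goes wrong, the immediate consequence is likely to be at work: dismissal or forced resignation, disciplinary action, involuntary loss of hours, pay or grade, or the diagnosis becoming known to people the participant did not want to tell. None of these is a medical outcome, and the only categories the protocol defines are medical.

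Two things are at stake. First, a participant could lose a job after a supported disclosure without any rule saying that this is an event to be classified and counted. Second, if such problems are heard of mainly through champions, they will be heard of mainly in the MSVR arm. People with MS can lose work whatever their allocation, so a count from one arm cannot show whether MSVR adds to the risk. The first failure would understate harm; the second could make MSVR look worse than usual care merely because only one arm was asked. Either would carry a poor basis for harm monitoring into the definitive trial. What counts as an event, and who is told of it, governs conduct while the trial runs, so it belongs in the protocol rather than the statistical analysis plan.

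**Working it through.** No arithmetic applies. The check sets the sections side by side and follows one case through them: a participant in the MSVR arm discloses the diagnosis with the champion's support and is dismissed soon afterwards, with no injury or hospital admission.

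1. **Is it an SAE?** There are five criteria: death, threat to life, hospital admission or its prolongation, lasting or significant disability or incapacity, and medical significance in the investigator's opinion. Dismissal as such meets none. The last criterion allows judgement, but judgement of medical significance.

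2. **Is it a RUSAE?** This category is a subset of SAE, so an event that fails step 1 fails here. Both examples are injuries.

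3. **Is there a lower category?** None is defined. The Table 2 row implies that adverse events are collected, but nothing says what falls within it.

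4. **Would it be heard of?** Possibly. The champions' prompt covers problems as well as accidents, so a dismissal is within its wording. But champions are encouraged rather than required to ask, and the protocol does not say what they then do with a non-serious answer. Under Intervention adherence and fidelity measures, the session form covers mode, topics, time per topic and time on follow-up actions; the summary form covers sessions completed, booked and cancelled. Neither is described as having a place for a problem at work.

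5. **Would it be heard of equally in the control arm?** Not through this route. Under Control Condition, controls deal with charity staff who are neither trained in MSVR nor involved in its delivery.

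6. **Would the outcome measures recover it?** They run in both arms at baseline and each follow-up, but none is described as recording dismissal, discipline or unwanted disclosure. As described, the work productivity measure covers time off, reduced performance and limits on activity; the accommodation items are yes/no questions on support received; goal attainment scores the participant's own goals. None includes a judgement of relatedness.

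7. **Would it be reported?** This depends on which sentence is followed. The RUSAE definition is limited to serious events, so the dismissal would not qualify. The later reporting sentence refers to an event without that limit, so on its literal wording a dismissal judged related and unexpected would go to the ethics committee. The two do not agree.

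In sum, the case fits none of the two defined categories, none of the five seriousness criteria and neither of the two examples. It may still surface through a prompt confined to one arm, or be reported under a sentence whose scope is unclear.

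**The case against.** The strongest reply is that the protocol is not blind to work problems. Champions ask about them in words wider than injury; questionnaires, ad-hoc CRFs and site notification are named as routes; and the reporting sentence, read literally, already reaches a related and unexpected dismissal. Monthly mentoring discusses cases and challenges, people who drop out are asked why, and the end-of-intervention interviews purposively include them. Employers are contacted only with the participant's consent. Safety is not among the aims, the feasibility outcomes in Table 1 or the progression criteria, so no safety conclusion is promised. The SAE definition is itself conventional, and losing a job does not become medically serious by widening it.

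Much of this stands. A reader might infer that an employment harm cannot be recorded at all, that the trial would report none whatever the true rate, and that nobody in charge would be alerted. The documents do not support that: the prompt, the routes and the reporting sentence each leave a way for such an event to come to light. Nor do they give any rate for such harms.

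What does not stand is that these routes close the gap. A route is no substitute for a definition of what to send along it. The prompt serves one arm. Mentoring and about ten interviews with participants can bring a case to light but do not give a count by arm. The reporting sentence repeats the related-and-unexpected test of the RUSAE definition and may only restate it; if it is meant more widely, it conflicts with that definition. The seriousness wording can stay as it is. What is missing is a non-serious category.

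**Conclusion.** The point holds in a limited form. The protocol defines events only by medical seriousness, leaves non-serious events undefined although Table 2 schedules adverse events, and delivers advice whose plausible harms are at work. Such harms meet no defined event and could go uncounted, or be ascertained in the MSVR arm only. The two descriptions of what is reportable also need reconciling.

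The size is qualitative, because the protocol holds no figure from which a frequency or a number missed could be derived. The conclusion rests on one judgement, that dismissal, discipline or loss of hours or pay is a plausible result of advice on disclosure, adjustments and career change, and on the measures doing no more than the protocol describes. If the participant questionnaires already contain an item on adverse changes at work, the gap narrows to the definition and the reporting wording. The change is worth making because it is cheap and makes the arms comparable; it does not call the design of the trial into question.

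**What to change.** In Reporting and management of adverse events:

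- Define a non-serious work-related adverse event: dismissal or forced resignation, disciplinary action, involuntary reduction of hours, pay or grade, or unwanted disclosure of the diagnosis. State that a grievance raised by the participant is not in itself a harm, since MSVR informs people of their legal rights and a grievance may be a proper use of them.
- Ask about it in both arms with one item in the existing participant questionnaires, with the same wording and time points.
- Record each event on the ad-hoc CRF already named, with date and short description. Have the PI judge relatedness, pass the events to the existing steering committee, and tabulate them by arm.
- Reconcile the RUSAE definition, limited to serious events, with the reporting sentence, which is not, and say which events each covers.
- Align the Table 2 row with the new definition and time points.

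The cost is one definition, one questionnaire item and a few words of reconciliation, with no extra visit or staff. The downside is a slight addition to questionnaire burden.

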**Methods and Analysis**

This is a multicentre, feasibility, parallel-group RCT with an embedded mixed methods process evaluation. Participants will be randomised (1:1 ratio) to receive either MSVR plus usual care (UC) or UC alone. This study will be reported following the CONSORT 2010 statement: extension to randomised pilot and feasibility trials [18].

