**Control Condition**

Participants (MS and employers) in the control group will receive resources from the MS charities' websites, helplines, and events. Due to the nature of the study, usual care will vary between participants in the control group. However, no MS charity recruited for this study will have a specialist vocational rehabilitation service (and none should have indicated that they will be creating such a post soon).

Participants (MS and employers) in the control group will interact with members from the MS charity who have not been trained and are not involved in MSVR delivery to reduce the potential for contamination.

At the end of the study, participants with MS in the control group will receive the “Work and MS: An Employee’s Guide” booklet from the MS Society, which contains information about MS and work. PPI representatives suggested this to reduce the burden of being allocated to the control group and encourage the completion of follow-up questionnaires.

*Concomitant Therapy*

Participants will continue to use services from social care, the National Health Service (NHS), and other third-sector organisations alongside MSVR. Information on any concomitant therapy received will be collected using a resource use questionnaire.

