**Outcome measures**

Outcomes measures will be assessed at the end of the intervention and 3-, 6-, and 12-months post-intervention. The measures collected and time points have been summarised in Table 2.

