Vocational goals will be measured using the goal attainment scale (GAS) [31] to ascertain the impact of the intervention on the vocational goals set by participants at the beginning of the study. Workplace accommodations will be assessed using a series of binary questions (yes/no) about support received at work.

Finally, a resource use questionnaire will be developed to record the healthcare utilisation and additional services and support accessed during the feasibility trial.

*Employers*

Employers will be asked to complete three questions regarding their knowledge of MS, confidence in managing the employee with MS at work, and confidence in their ability to solve future problems at work.

*MSVR Champions*

MSVR champions will be asked to complete the educational course assessment toolkit (EDUCATOOL) [32]. A 12-item questionnaire to evaluate the training and learning experience of the MSVR champions during the study.

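### Adverse events are said to come from participant questionnaires, but Table 2 schedules them only during the intervention, where no questionnaire is given, and the one described prompt reaches the MSVR arm alone

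*Protocol*

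**What the plan says.** The Protocol deals with harm in two main places.

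- **Reporting and management of adverse events.** On prompting: "MSVR champions will be encouraged to discuss with participants whether they have experienced any problems or accidents at work". The rest of that sentence ties the enquiry to what participants were told as part of MSVR. On sources, after defining related unexpected serious events: "This data will be collected by self-report (participant questionnaires and ad-hoc CRFs, or via sites notifying a member of the research team". The section gives two examples of such events: injury from a workplace adaptation that a champion recommended, and a workplace accident needing hospital treatment.
- **Table 2.** The adverse event row reads "Adverse events | | | x". The tick falls in the Intervention column, and the four later columns are empty.

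Three other passages bear on who is asked and when.

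- **Control Condition.** Control participants "will interact with members from the MS charity who have not been trained and are not involved in MSVR delivery".
- **Intervention: MSVR.** On duration: "the intervention was extended to support the person with MS over six months".
- **Outcome measures.** On timing: "Outcomes measures will be assessed at the end of the intervention and 3-, 6-, and 12-months post-intervention".

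**The concern.** The text relies on participant questionnaires, but the schedule has no questionnaire at the one point where adverse events are ticked, and no adverse event tick at the points where questionnaires are completed. A team that builds its REDCap forms from Table 2 would have no adverse event item in any scheduled questionnaire.

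That would leave the champions' enquiry as the only described prompt, and it reaches one arm. Spontaneous reports and site notification are open to both arms, but MSVR participants also have individual sessions with someone encouraged to ask. More events could be recorded under MSVR simply because those participants are asked.

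Timing raises a separate problem. A workplace adaptation can stay in use after support ends, so an injury of the kind the protocol foresees could fall in the 12 months for which no adverse event collection is scheduled. The expedited reporting to the ethics committee can start only once the team has heard of an event.

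**Working it through.** The protocol gives no event rate, power or error rate for harm, so there is no figure to reproduce. The check sets the passages side by side, with simple schedule arithmetic.

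**Step 1: where the questionnaires are.** In Table 2 the participant-completed measures are ticked at baseline, end of intervention (A2), and 3, 6 and 12 months. That makes 4 post-baseline questionnaires. The Intervention column holds ticks only for adverse events and intervention cost.

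**Step 2: where adverse events are.** They have one tick, under Intervention. Post-baseline questionnaires with an adverse event tick: 0 of 4. The neighbouring rows fall where one would expect (intervention cost under Intervention, interviews at end of intervention), so the tick does not look misplaced.

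**Step 3: whether a listed instrument carries the item.** The Outcome measures section and Table 2 name SF-36, the work productivity questionnaire, EQ-5D-5L, PDQ, the fatigue scale, the self-efficacy scale, GAD-7, PHQ-8, GAS, workplace accommodation questions and the resource use questionnaire. None is described as recording adverse events. The nearest is the last: "a resource use questionnaire will be developed to record the healthcare utilisation and additional services and support accessed during the feasibility trial". It could reveal a hospital contact, but it is not described as asking about injury or relatedness to the intervention.

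**Step 4: who is prompted.** With "Participants will be randomised (1:1 ratio) to receive either MSVR plus usual care (UC) or UC alone", half the sample is allocated to MSVR and meets champions. The Control Condition section keeps the other half with staff outside MSVR delivery, and no matching prompt is described for them. The champions' route is itself loose: they are encouraged, not required, to ask. The content form described under Intervention adherence and fidelity measures covers modality, topics, time and follow-up actions, with no adverse event field mentioned.

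**Step 5: time covered by the schedule.**

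- Intervention period: 6 months.
- Follow-up after it: 12 months.
- Total: 6 + 12 = 18 months.
- Marked for adverse events: 6 / 18 = 33%.
- Not marked: 12 / 18 = 67%.

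**Step 6: scope of the self-report sentence.** It follows the paragraph on related unexpected serious events. It is unclear whether it covers all adverse events or only the serious ones.

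**The case against.** The strongest case on the other side has four parts.

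1. **Other routes exist in both arms.** Self-report, ad-hoc CRFs and site notification are not restricted by arm, and questionnaires go to everyone. This stands. A reader might infer that only champions ever ask about harm, or that usual care has no collection at all. The text does not support that: it names questionnaires as a source but does not say which one or when.
2. **The champions' enquiry is specific to the intervention.** It concerns problems arising from MSVR advice, which controls do not receive, so some one-sidedness is natural. This stands in part. The section also names workplace accidents needing hospital treatment, and a serious event such as a hospital admission can occur in either arm.
3. **No comparison of harm is planned.** The aims, outcomes, progression criteria and data analysis sections contain none; the trial has 60 participants and serious events are not anticipated. How events are tabulated may properly be left to the SAP. This stands, and it limits the weight of the point. It does not remove it, because a SAP cannot recover events that were never asked about, and this study exists to test procedures for a larger trial.
4. **The resource use questionnaire would catch some events.** It is scheduled in both arms at every assessment and could reveal hospital contact. This stands as a partial safeguard only, for the reason given in step 3 of the working.

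**Conclusion.** The inconsistency is real. The adverse event section depends on a questionnaire route that Table 2 does not schedule and that no listed instrument is said to carry. The one described prompt reaches only the MSVR arm. The schedule marks 6 of 18 months and none of the four post-baseline questionnaires. Any listing of events by arm would be open to unequal ascertainment, most likely towards more recorded events under MSVR during the intervention, and late related events could be missed in that arm.

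Two stronger readings are not supported. One is that the arms cannot be compared for harm: a comparison would be exposed to bias, but routes open to both arms exist, and the protocol does not state such a comparison as an aim. The other is to size the problem as the share of participant-months in contact with a champion. That would give no weight to questionnaires, CRFs and site notification, and would assume that champions ask throughout. The size of any bias, or the number of events missed, cannot be derived from the document.

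The conclusion assumes that Table 2 governs what is built into the questionnaires and that its Intervention column means the six-month support period. If an adverse event item is already planned for the questionnaires, the correction reduces to stating that and completing the table. The change should be made, but no stated aim or progression decision depends on it.

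**What to change.** Reconcile Table 2 with the adverse event section as follows.

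- Put the same adverse event and serious adverse event item, with the same wording and recall period, in the A2, 3-, 6- and 12-month questionnaires for both arms.
- Tick those four columns in the adverse event row of Table 2, and name the item in the Outcome measures section.
- State whether the self-report sentence covers all adverse events or only serious ones.
- Base any summary by arm on the questionnaire answers. List champion-prompted reports separately, labelled as a source available only in the MSVR arm.

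The cost is one item in four existing questionnaires, a table edit and a few more reports to review. REDCap collection, with blinded telephone or postal collection as the alternative, is already planned, so no new contact with participants is needed.

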**Introduction**

Multiple Sclerosis (MS) is the most common chronic neurological condition affecting young adults [1]. Women are two times more likely to develop MS than men, and currently, MS affects over 150,000 people in the UK [2]. People are usually diagnosed between 20 and 40 years of age, the prime working years of an adult [3].

MS is characterised by progressive damage to the Central Nervous System (CNS), producing plaques in the brain and spinal cord [4]. These lesions are caused by the loss of myelin sheaths which leads to inflammation and axonal damage (or loss) [1].

Due to the damage to the brain, people with MS can present with a range of physical and cognitive problems. The most common physical problems presented in MS are gait difficulties that can lead to people needing a wheelchair and balance disorders, which lead to an increased risk of falls [5]. In fact, after 15 years with the condition, approximately 50% of people with MS need support walking [6].

Furthermore, up to 65% of people with MS present some level of cognitive impairment [7]. Although significant variability exists in the types and intensity of impairments MS can cause, memory and attentional problems are the most frequently reported in this population [7–9].

To this array of physical and cognitive impairments, MS is also characterised by the presence of “invisible symptoms”, which are symptoms not visible to others. Some invisible symptoms are fatigue, pain, bladder and bowel problems, and vision difficulties, among others [10]. From these, fatigue is the most reported symptom in MS (approximately 90% of people with MS) [11].

The range of physical, cognitive, and psychological problems that people with MS can present increases the personal and professional challenges that people with MS experience at work [12].

Vocational rehabilitation (VR) aims to help people with illness or disabilities to remain, return to or find new employment. We have previously developed a VR intervention to support people with MS to remain in paid employment called MSVR (multiple sclerosis vocational rehabilitation) [13]. We have tested this programme in a community setting [14], and within the NHS [15]. However, we found barriers (e.g., lack of staff, service structure, etc.) to deliver this programme within a healthcare setting [15,16]. Patient and public involvement (PPI) representatives suggested testing this programme within the services provided by MS charities.

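### The only active adverse-event question is narrower than the SAE definition, so serious events risk being under-ascertained

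*Protocol*

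**What the plan says.** All the operative text is in the protocol section on reporting and management of adverse events.

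- **Definition.** An SAE is "any untoward occurrence that results in death, is life-threatening, requires hospitalisation or prolongation of existing hospitalisation", together with the remaining seriousness criteria. Neither cause nor place is a condition.
- **Expectation.** "Due to the nature of the intervention, we do not anticipate SAE".
- **Active enquiry.** Champions are encouraged, not required, to discuss with participants "whether they have experienced any problems or accidents at work based on the information provided during the intervention".
- **Relatedness.** This is a separate, later step: a related unexpected SAE (RUSAE) is one where, "in the opinion of the Principal Investigator (PI), the event was considered to be" both related and unexpected.
- **Other routes.** "This data will be collected by self-report (participant questionnaires and ad-hoc CRFs, or via sites notifying a member of the research team").

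Table 2 marks adverse events in the Intervention column only and lists no adverse-event questionnaire at any assessment. The Control Condition section says that control participants deal with charity staff who are not involved in delivering MSVR.

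**The concern.** The definition and the question do not match. The definition takes in any serious event. The question takes in only events at work and, as most readers would parse it, only those that arose from what the champion had told the participant. A participant who answers it literally must settle a causal question before mentioning the event, although the protocol keeps that question for the PI.

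A fall at home, or an admission that the participant does not connect with the advice, meets the definition but is not asked about. Nor are harms confined to the workplace: MSVR covers disclosure, mood and career planning, so even a related event could appear elsewhere.

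The trial is meant to inform a definitive RCT. If few or no SAEs are reported, readers will not be able to tell whether few occurred or few were asked about.

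**Working it through.** The protocol states no figure on this point, so there is none to reproduce. The check is mainly a comparison of the texts.

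**1. Scope of the definition against scope of the prompt**

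| Feature | SAE definition | Champion prompt |
| --- | --- | --- |
| Place | any | at work |
| Cause | any | tied to MSVR information (natural reading) |
| Who judges cause | the PI, afterwards | implicit in the answer |
| Arm reached | both | MSVR only |

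The prompt is narrower on place under any reading, and narrower on cause under the natural one.

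**2. Fit with the section's own example.** One event the section offers as a possible RUSAE is "workplace accidents resulting in injury requiring hospital treatment", with no stated link to advice. On the natural reading, the prompt elicits such an accident only if the participant has already made that link.

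**3. Fit with the stated expectation.** The nature of the intervention is a reason to expect no *related* SAEs. It is no reason to expect no SAEs of any cause in a disease that the Introduction describes as progressive and associated with "balance disorders, which lead to an increased risk of falls".

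**4. Whether the other routes make up the difference**

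- The sentence naming them follows the RUSAE paragraph, so the data it refers to may be RUSAEs only.
- Table 2 lists no adverse-event instrument among the participant questionnaires.
- Ad-hoc CRFs and site notification need someone to learn of the event first, and the champion conversation is the one described way of asking.
- The resource use questionnaire records healthcare utilisation at baseline, end of intervention and 3, 6 and 12 months. It has still to be developed and is not named as a safety source.

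**5. Size within the prompt's own reach**

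- Inputs: 30 participants in the MSVR arm (Sample size section); six months of intervention (Intervention section).
- Person-years: 30 × 0.5 = 15.
- Assumed all-cause admission rate: 5-15% per year. The protocol gives no rate.
- Expected admissions: 15 × 0.05 = 0.75 to 15 × 0.15 = 2.25.

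This is the number expected among the people whom the prompt reaches. It is not an estimate of events lost, because some may be work-related and linked to advice, and others may arrive by another route.

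**The case against.** The strongest reply is that the champion conversation is an optional extra and not the whole system. The section names questionnaires, CRFs and site notification, none of them limited to work or to attributed events, and the resource use questionnaire could show an admission. This stands in part. It rules out the stronger reading a reader might take, that unattributed events are filtered out and never reach the PI. It does not show that the gap is closed, for the reasons in step 4 of the working.

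A second reply is that the qualifying phrase is ambiguous and may describe the basis of the conversation, not the cause of the problem. The section's separate mention of workplace accidents lends this some support. Even so, the restriction to work remains, and a prompt that champions can read in two ways will be applied unevenly.

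A reader might also infer that the champion who gave the advice makes the causal judgement. The text does not say so: champions discuss, and only the PI is given relatedness. Any attribution lies in how the question is framed for the participant.

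Finally, safety is neither a progression criterion nor listed among the feasibility outcomes in Table 1, and the sentence on anticipated SAEs can be taken to mean events arising from MSVR. Both points are fair. They limit the weight of the finding and make the change to that sentence a clarification, but they do not reconcile the prompt with the definition.

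**Conclusion.** The point holds as a risk of under-ascertainment. The stated enquiry conflicts with the stated definition, and the protocol does not show that its other routes compensate. This is a rule that is fixed badly, not a detail left to another document.

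The scale is modest: about 0.75 to 2.25 admissions expected in the MSVR arm during delivery, resting wholly on the assumed 5-15% annual rate. The conclusion does not depend on that figure, since the mismatch is in the wording. It would be wrong to extend the arithmetic to all 60 participants or to the follow-up period as a measure of this defect, because the prompt reaches neither the control arm nor the period after delivery. The protocol also makes no claim to bound an event rate from a nil count, so none needs rebutting.

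**What to change.** 1. Reword the champion prompt to be neutral on cause and place: any hospital admission, injury, accident or other event meeting the SAE definition since the last contact, at work or elsewhere.
2. Have champions record what is reported without attributing it. Leave relatedness to the PI, as the section already provides.
3. Put the same question in the scheduled participant questionnaires and show it in Table 2, so that both arms are asked alike. Broadening the champion prompt alone would make ascertainment differ by arm, since control participants have no champion.
4. Say whether the sentence on self-report covers all SAEs or only RUSAEs.
5. Limit the statement on anticipated SAEs to related SAEs.

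The cost is one reworded prompt, one added questionnaire item, a changed row in Table 2 and two clarified sentences. The downside is a few more unrelated events to log and pass to the PI.
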